#### Ulcer area

Surface area of the ulcer, expressed in square centimetres and measured at baseline and at weeks 5 and 9, using the ImageJ software to analyse photographs taken at these time points.

#### CIVIQ score

Score on this specific scale for assessing the quality of life of patients with chronic venous insufficiency, considering four dimensions (physical, psychological, social and pain). This secondary variable will be measured using a questionnaire for the patient, yielding a score between 20 corresponding to the lowest quality of life, and 100, the best quality of life. The questionnaire will be administered and the score recorded by the nurse in the baseline treatment session, and again at weeks 5 and 9.

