**Study algorithm.**

Patients will have an appointment in the health center; they will be seen by a doctor of the centre, who will carry out an interview to collect data related to the selection check list, and they will be weighed, their height measured, and a ABI test will be performed. If the patient meets the inclusion criteria, they or their legal guardian will be asked to give verbal and written informed consent before inclusion in the clinical trial, and after a “Patient Information Sheet for research projects involving the use of biological samples” has been provided and explained to them, by the principal investigator.

Once patients give informed consent, the doctor will contact the Primary Care Research Unit of Bizkaia to request that the patient be randomly allocated to the control or intervention group, and their inclusion in the study will be reported to their general practitioner. The patient’s wound will be cared for as usual, and they will be given a patient handbook including a diary to keep a daily record of their experiences and any adverse effects, and an appointment will be made for their first treatment as part of the study, either using autologous PRP or under the MWC protocol, depending on their group allocation. The patient handbook also includes a telephone number they should call in the event of any unforeseen problems between treatments.

In the event that there is no record in a patient’s medical record of a blood test having been performed in the 6-months prior to inclusion in the study, the general practitioner will request a blood test, the results of will be taken as the baseline measurement.

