### Protocol

#### Control group

Patients in the control group will be treated as they had been prior to inclusion, that is, two to three times a week and in accordance with the health region recommendations, namely to maintain a moist healing environment. The wound care will consistently be provided by the same nurse, who will be responsible for making the appointments within the available timetable in the treatment room. The data will be registered in an Access database by the administrator. The treatment schedule for the control group is displayed in Tables 1 and 2.

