### Intervention group

Patients in the intervention group will receive wound care once a week with autologous PRP, based on the estimated mean lifespan of platelets (7–10 days). The treatment with autologous PRP will be performed in the assigned outpatient clinic, in the phlebotomy room, by qualified nurses ([name]).

As in the control group, the nurse will be responsible for making appointments for the next treatment and will collect data to be entered in an Access database by the administrator. The first treatment session of the study will be performed on day 8, and the data will be recorded in the patient medical record. From this point onwards, data will be collected every 7 days for 9 weeks. Treatment schedule for the PRP group is shown in Table 2.

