### Limitations of the study

Taking into account that the treatment applied to both groups consists initially of a topical treatment, with significant differences in the appearance of the dressing to be applied, patients will be aware of their group allocation, as will the researchers, meaning that it is not feasible to double blind the study. To prevent the results of the research being influenced by observer bias, the progress of the ulcers will be assessed by someone independent of the research team, who will have exclusive access to photographs of the ulcers, with no type of identifying data related to the patient or their group.

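### Baseline CIVIQ is taken after open-label randomisation, and the nurses who administer it differ by arm, with no safeguard for this outcome

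*Protocol article*

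**What the plan says.** **Who handles the questionnaire.** The CIVIQ score section describes a patient-reported measure: "This secondary variable will be measured using a questionnaire for the patient". It then assigns administration and recording to a nurse: "The questionnaire will be administered and the score recorded by the nurse in the baseline treatment session". The same is to happen at weeks 5 and 9.

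**Which nurse.** For controls, "The wound care will consistently be provided by the same nurse", working in the treatment room. For the intervention arm, PRP is given by qualified nurses in the phlebotomy room of the assigned outpatient clinic. There, as in the control group, "the nurse will be responsible for making appointments for the next treatment and will collect data".

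**When.** The Study algorithm text gives the order: "Once patients give informed consent, the doctor will contact the Primary Care Research Unit of Bizkaia to request that the patient be randomly allocated". The first study treatment is then booked according to the arm assigned. Tables 1 and 2 mark randomisation on Day 1. The Intervention group section adds: "The first treatment session of the study will be performed on day 8".

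**Blinding.** Limitations of the study states that "patients will be aware of their group allocation, as will the researchers". The one safeguard described there is an independent assessor who sees only de-identified ulcer photographs.

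**The concern.** CIVIQ is a subjective outcome in an unblinded trial. Two features of its collection are avoidable.

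- **Timing.** A baseline should describe patients before allocation can influence them. If the first score is taken after the patient knows the arm, hope or disappointment can move it differently in the two groups.
- **Handling.** If one set of nurses administers the form in one arm and another set in the other, any influence of the person or the setting is tied to treatment. It cannot be separated from a treatment effect.

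Quality of life is not incidental here. The Background gives it, alongside healing, as a reason for the trial, and it has its own bullet under Secondary objectives. The protocol recognises observer bias as a threat, but protects only the photographic outcome.

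**Working it through.** No stated figure is disputed, so there is none to reproduce. The check sets the passages side by side and then asks what can be said about size.

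**1. Timing of the baseline.** Randomisation is on Day 1 (Tables 1 and 2). The first study treatment session is on Day 8 (Intervention group). The gap is 8 − 1 = 7 days. The Day 8 sentence refers to the PRP arm. For controls, Day 8 is inferred from the Ulcer Assessment row, which is marked on Days 8, 36 and 64 in both tables and so matches baseline, week 5 and week 9. Neither table has a CIVIQ row. Table 1 is titled for the control group but carries the PRP treatment row, so it must be reconciled with the control-group text. The protocol does not say whether CIVIQ precedes the first PRP application.

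**2. Who administers it.** The CIVIQ section says the nurse and places the questionnaire in the treatment session. The group sections assign care and data collection to that session's nurse. That this is the treating nurse is a strong inference, not a statement in the text. Staff and setting then differ by arm.

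**3. Safeguards.** The masked assessor reads photographs only. Nothing comparable is described for CIVIQ.

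**4. Direction of bias.** Let b0 and b1 be the between-arm shifts in reported score, unrelated to true benefit, at baseline and at follow-up.

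- Follow-up scores compared directly: bias = b1.
- Change from baseline: bias = b1 − b0.
- Baseline-adjusted model with slope k: bias = b1 − k × b0.

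A constant influence (b0 = b1) cancels in a change score. A lift already present in the PRP baseline (b0 > b1) makes PRP look worse. The sign is therefore not determined. The algebra also shows that moving the baseline before allocation sets b0 to 0 but leaves b1, so the follow-up handling has to change as well.

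**5. Illustration of size (bias and SD both assumed).** The documents give no CIVIQ SD. Take 15 to 20 points on the 20–100 scale. Evaluable patients per arm: 75 × (1 − 0.30) = 52.5 (Sample size section). For a direct follow-up comparison with no true effect:

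nc = b1 / (SD × √(2/52.5)); error rate = P(|Z + nc| > 1.96)

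| Assumed SD | SE of difference | b1 = 3 points | b1 = 5 points |
|---|---|---|---|
| 15 | 2.93 | nc 1.02, 17.6% | nc 1.71, 40.1% |
| 20 | 3.90 | nc 0.77, 12.0% | nc 1.28, 24.9% |

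In SD units, shifts of 0.1, 0.2 and 0.3 SD give about 8%, 18% and 33% with 52 per arm, and 9%, 23% and 45% with 75 per arm. These figures show sensitivity to an assumed shift. They do not estimate what would happen in this trial.

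**The case against.** The strongest reply has five parts.

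- **Recorded is not scored.** A reader might infer that the nurse rates the patient's quality of life. The text does not support that: it describes a patient questionnaire whose score the nurse records, and administering could mean handing out a form. The Safety section speaks of a nurse interview; the CIVIQ section does not. This stands, so the concern is influence through administration and not nurse judgement.
- **Expectation bias is unavoidable and the lack of blinding is disclosed.** A reader might infer that better handling of CIVIQ would remove it. It would not, because patients still know their arm at weeks 5 and 9. This stands for follow-up, but not for the baseline, whose timing is a free choice.
- **The error rates prove little.** A reader might take 12% to 40% as the trial's false-positive risk. The shifts and SDs are assumed, and a constant influence would partly cancel after baseline adjustment. This stands.
- **No adjusted CIVIQ analysis is stated.** The Statistical analysis section describes its comparison, and the covariance models that follow, for percent reduction in ulcer area. A reader might infer that the plan commits to adjusting CIVIQ for a contaminated baseline. It does not say so.
- **Day 8 is a reasonable baseline close to the start of treatment.** This has some force, but a pre-allocation score is available at a visit that already exists.

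It is also true that no hypothesis or sizing is stated for CIVIQ, which limits the weight of the point.

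**Conclusion.** The concern holds as a cheap improvement to a secondary outcome. As written, the baseline of a subjective measure follows an allocation the patient knows, by seven days. Administration sits with nurses who differ by arm, and the masking does not reach this outcome. The conclusion rests on two strong inferences: that the nurse in the CIVIQ section is the one running the treatment session, and that the control baseline, like the PRP baseline, is on Day 8.

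Neither the size nor the direction of bias can be derived from the documents. The documents do not support reading this as a defect that invalidates the trial: the primary outcome is measured from photographs by a masked assessor and is unaffected.

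**What to change.** - Collect baseline CIVIQ at the Day 1 visit, after consent and before the allocation request.
- At Days 36 and 64, have the patient complete the form alone before wound care. The treating nurse should neither read out nor answer items.
- Record the mode of completion and any help given, including by whom. A relative who helps is not neutral, since that person may know the arm.
- Add a CIVIQ row to both timetables, and reconcile Table 1 with the control-group text.
- State as a limitation that CIVIQ at follow-up remains open to patient expectation, which the open-label design cannot remove.

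**Cost.** A short protocol change using visits that already exist. Some older patients will need help and a few items may be missing. The protocol does not say who other than the treating nurse could assist at each centre, so centres would have to name someone.

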#### Safety

Will be assessed in terms of any adverse effects recorded by patients and by the weekly interview carried out by the nurse, who will ask about the pain, assess the degree of infection and the type of exudates, as well as any adverse effects associated with the treatment, comparing with the results in the control group.

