### Secondary objectives

To assess the safety of autologous PRP for the treatment of venous ulcers in patients with chronic venous insufficiency corresponding to C6 on the CEAP classification (C, clinical class, E, aetiology, A, anatomy and P, pathophysiology of the disease), describing changes in patient perceived pain, the percentage of ulcers with infection, and related perilesional changes, in both groups and comparing the results.

• To estimate the quality of life of patients in terms of the Chronic Venous Insufficiency Quality of Life Questionnaire (CIVIQ) score in both groups at baseline, and 5 and 9 weeks after starting the treatment.

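### Perilesional changes are a stated safety comparison with no defined measurement, and infection is graded unmasked by a nurse who probably differs by arm

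*Protocol article*

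**What the plan says.** All references are to the protocol article.

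- **Secondary objectives.** Safety is to be assessed by "describing changes in patient perceived pain, the percentage of ulcers with infection, and related perilesional changes, in both groups and comparing the results".
- **Outcome measures, Safety.** Safety "Will be assessed in terms of any adverse effects recorded by patients and by the weekly interview carried out by the nurse". That interview is "carried out by the nurse, who will ask about the pain, assess the degree of infection and the type of exudates", together with adverse effects linked to treatment, for comparison with control.
- **Adverse effects.** The nurse asks about adverse effects at every appointment and records severity and possible relationship to treatment. An independent committee monitors safety and reviews events that arise.
- **Control group.** Patients are seen two or three times weekly. "The wound care will consistently be provided by the same nurse", in the treatment room.
- **Intervention group.** PRP care is weekly and "will be performed in the assigned outpatient clinic, in the phlebotomy room, by qualified nurses".
- **Limitations of the study.** Patients and researchers know the allocation. Against observer bias, "the progress of the ulcers will be assessed by someone independent of the research team", using photographs without identifying data.
- **Ulcer area.** Photographs are taken at baseline and weeks 5 and 9, and their stated use is area measurement.

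**The concern.** The Discussion describes efficacy and safety as the study's two main objectives, so the safety comparison carries weight. Three features weaken it.

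1. An outcome that the objectives promise to compare has no counterpart in the itemised collection list.
2. Infection is a bedside judgement by someone who knows the treatment. The plan protects ulcer progress from exactly this kind of observer bias but does not extend the protection to infection.
3. With no perilesional item of its own, that outcome falls back on adverse-effect questioning, whose frequency depends on the arm.

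At stake is whether a difference, or a lack of one, in infection or perilesional skin can be put down to treatment rather than to who looked and how often. Under Reasons for withdrawal from the trial, infection signs also lead to a decision on whether the patient continues, so infection judgement can affect who remains under observation.

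**Working it through.** The plan gives no figure for the safety comparison, so there is none to reproduce. The total of 150 patients in Sample size plays no part here. The check is mainly a comparison of sections, plus one count.

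**Step 1: objective against collection list.**

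| Secondary objectives | Safety section | Agreement |
|---|---|---|
| Pain | Pain | Yes |
| Infected ulcers, as a percentage | Infection, as a degree | Same topic, different scale; no cut-off stated |
| Perilesional changes | No item | None |
| No item | Exudate type | Added in Safety |

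**Step 2: is perilesional skin measured elsewhere?** The other outcome sections cover ulcer area, its percent reduction and the CIVIQ score. Assessment of surrounding skin appears only under Moist wound care, where it guides the choice of dressing for control patients. That is not an outcome record and applies to one arm.

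**Step 3: is infection graded masked anywhere?** The nurse's grade is unmasked. The masked reader is assigned ulcer progress. The safety committee is independent, but it is not said to be masked or to grade infection. The diary is kept by patients who know their treatment. No section gives a masked infection grade.

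**Step 4: does the assessor track the arm?** Control patients have one consistent nurse in the treatment room. PRP patients are treated by qualified nurses in the phlebotomy room of the assigned clinic. Different staff by arm is the likely reading, but the text does not rule out one nurse serving both.

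**Step 5: opportunities to report an adverse effect.**

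- PRP sessions in Table 2: days 8, 15, 22, 29, 36, 43, 50 and 57, which is 8 contacts.
- Control over the same 8 weeks, from the Control group text: 2 × 8 = 16 to 3 × 8 = 24 contacts.
- Ratio: 16/8 = 2 to 24/8 = 3.

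The control figure comes from the text because Table 1, headed as the control timetable, repeats the PRP rows of Table 2. The PRP count is the planned schedule. A note under the tables mentions treatment every 48 to 72 hours in certain weeks, but its marker is attached to no column in the text at hand. If it applied to PRP weeks after day 8, the imbalance would shrink.

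The infection item belongs to an interview described as weekly, so the contact imbalance bears on adverse effects, and through them on perilesional events, rather than directly on the infection grade.

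**The case against.** The strongest reply has four parts.

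- **The article condenses.** A one-sentence safety description need not list every field on the nurse's form. This has force: the form may contain a perilesional item. But the article does give a list, and that list differs from its own objective in both directions, with one item missing and one added.
- **Perilesional events can still be captured.** A reader might infer that the trial will hold no perilesional data. The documents do not support that. Such events may be entered as adverse effects by the nurse or in the patient's daily diary, or be visible on photographs, and adverse effects are recorded up to 30 days after treatment stops. What is lacking is a defined measurement made equally in both arms.
- **Separate nurses are an inference.** A reader might conclude that assessor and arm are completely confounded. The continuity described for control does not say that the nurse never treats PRP patients, and different rooms do not prove different people. Only probable confounding can be claimed. The unmasked grading stands either way.
- **Open-label bedside grading is ordinary and disclosed.** True, and the plan is candid that blinding is not feasible. But it already has a masked reader looking at these ulcers, so a partial check costs little.

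It is also tempting to put a size on the bias. Assuming a true infection rate of 10% in both arms and misgrading of 10% to 20% in opposite directions gives 9% against 11%, up to 8% against 12%. Neither assumption comes from the documents. Even the larger gap of 4 points lies below one standard error of the difference with 75 per arm: √(2 × 0.1 × 0.9 / 75) = 4.9 points. The illustration is not evidence for the point.

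Finally, a reader might want the photographs to become the main safety comparison. That would be worse than the present plan. Three time points miss infections that come and go between them, patients withdrawn for infection may have no later photograph, and nothing says the frame includes surrounding skin.

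**Conclusion.** The point holds in a limited form. Secondary objectives and Safety disagree: perilesional changes have no defined measurement, and infection is a proportion in one place and a degree in the other. Infection grading is unmasked and probably, not certainly, done by different nurses in the two arms. If perilesional events are caught only as adverse effects, planned opportunities to report them are two to three times as many in control (16 to 24 against 8 over eight weeks). With equal true rates, that would tend to make PRP look safer.

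This rests on the visit frequencies in the group descriptions applying throughout, and on the nurse's form holding no perilesional item beyond the published list. The size of any resulting bias in event rates cannot be derived from the documents. The efficacy comparison of ulcer area is not affected by this point. It is a worthwhile, inexpensive improvement, not a flaw that invalidates the trial.

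**What to change.** 1. Align the Safety section with Secondary objectives. Add perilesional changes (present/absent) and infection (present/absent) to the weekly nurse record, with the degree of infection kept alongside.
2. Complete these items on the same weekly schedule in both arms, so that additional control visits do not add assessments to the comparison.
3. Keep this nurse record as the main between-group safety comparison, and count infections that lead to withdrawal as events.
4. As a supportive check, have the masked assessor already described under Limitations of the study score visible infection signs and perilesional skin from the baseline, week 5 and week 9 photographs, where the frame allows. Report this beside the nurse-graded result.

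The cost is a few extra fields on the nurse form and on a reading that is already planned. The limit of step 4 is that photographs show only visible signs, at three time points, in patients still being followed. It therefore supplements the nurse record and does not replace it.

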### Adverse effects

At all of the appointments during the study period, the nurse will ask the patients whether they have experienced any adverse effects. Any effects identified will be recorded by the nurse himself/herself in the database created for the purpose, with the following data: severity and potential relationship with the study treatment. In addition, there will also be a committee independent of the research team that will monitor the safety of the treatment under study and review any adverse events that do arise during the study.

Complying with the current legislation, any serious adverse reaction (SAR), or unexpected serious adverse reaction, (USAR) will be reported to the health authorities within 24 hours of being detected.

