**Table 2 Tab2:** **Timetable for the intervention group**

**Activities**	**Recruitment Day 0**	**Selection Day 1**	**Day 3**	**Day 5**	**Day 8**	**Day 15**	**Day 22**	**Day 29**	**Day 36**	**Day 43**	**Day 50**	**Day 57**	**Day 64**
Patient recruitment	X												
1^st^ visit		X											
Leg Doppler ultrasound		X											
Informed consent		X											
Randomisation		X											
Inform GP in writing		X											
Conventional treatment		X	X	X									
Autologous PRP treatment					X	X	X	X	X	X	X	X	
Ulcer Assessment					X				X				X
Final Assessment													X

Week^(1)^: the wound will be treated every 48 to 72 hours during these weeks, as required in each case (depending on the condition of the ulcer).

Week^(1)^: the wound will be treated every 48 to 72 hours during these weeks, as required in each case (depending on the condition of the ulcer).

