### Moist wound care

Patients in the control group will be treated following the recommendations for MWC of Osakidetza (described in the rational use of the moist wound care products section of the Osakidetza 2011 continuous professional education guide). Material is selected for wound care depending on the assessment of the bed of the wound and surrounding skin, as well as the type and amount of exudate and whether there are signs of infection. These wound care treatments will be carried out every 48–72 hours, in line with the current usual practice.

There are multiple types of dressings, each of which have a proposed indication as well as certain known advantages and disadvantages. It is important to recognise that no single dressing is suitable for all types of ulcers and few are indicated for all stages of healing. For a given wound, the ideal dressing should absorb excess exudate, create a moist environment, and maintain an adequate pH, while also being thermally insulating, impermeable to bacteria and easy to change, as well as not causing allergic reactions or damage when removed.

The materials used in the MWC include the following:Debriding agents: enzymatic, mechanical, physiological and autolyticAntimicrobial agents: containing silver, indicated for infected woundsActivated charcoal: for odour controlHydrocolloids: for debridement and promotion of granulation tissue, one of their strengths being that they are not very absorbent.Alginates and hydrofibres: for exudating and contaminated wounds and they also have a hemostatic effect; a disadvantage of alginates being that they are less absorbent than hydrofibresPolyurethane foams: hydrocellular dressings and hydropolymer dressings; the latter are indicated for moderate to high amounts of exudate, but their disadvantages include that they do not absorb exudates or debride the wound in the same way.Barrier products: for preventing maceration and irritation of the skin around the lesion

When selecting a dressing, as well as the characteristics of the wound, it is necessary toassess the general status of the patient, the availability of resources, and the cost-effectiveness of alternatives, as well as how easy it is to apply.

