### Follow-up period

The follow-up period will last for 9 weeks, but all the adverse effects that appear within 30 days of stopping the treatment will be recorded.

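### The protocol gives two conflicting rules for how often adverse effects are elicited, one of which differs by arm, and its 30-day collection window has no stated starting point for controls

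*Protocol article*

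**What the plan says.** Two sections of the protocol article set the frequency of safety questioning.

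- **Adverse effects:** "At all of the appointments during the study period, the nurse will ask the patients whether they have experienced any adverse effects". The nurse records whatever is found, with its severity and possible relation to treatment.
- **Safety (under Outcome measures):** safety is judged from effects recorded by patients and "by the weekly interview carried out by the nurse, who will ask about the pain". At that interview the nurse also assesses infection and exudate, and the results are compared with the control group.

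Appointment frequency depends on the arm.

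- **Control group:** patients are treated as before inclusion, "that is, two to three times a week".
- **Moist wound care:** "These wound care treatments will be carried out every 48–72 hours, in line with the current usual practice".
- **Intervention group:** "Patients in the intervention group will receive wound care once a week with autologous PRP".
- **Footnote printed under Table 2, the intervention timetable:** "the wound will be treated every 48 to 72 hours during these weeks, as required in each case". As shown, no cell of the table carries its marker.

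Every randomised patient also receives a handbook with a daily diary for adverse effects and a telephone number (Study algorithm). On the end of collection, Follow-up period says that "all the adverse effects that appear within 30 days of stopping the treatment will be recorded". It does not name an arm.

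**The concern.** Comparing safety between arms is a secondary objective, and the Discussion calls safety one of two main objectives. If the comparison uses everything recorded at every appointment, the number of chances to report an event depends on allocation. The arm questioned more often tends to record more events even when the true rates are equal. Here that arm is the control arm, so this mechanism flatters PRP.

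Little else protects this outcome. The trial is open-label, and the independent assessor described under Limitations sees only ulcer photographs. The control timetable does not settle the matter, because Table 1 prints the same PRP treatment row as Table 2.

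The 30-day window raises a separate problem. Control care continues usual practice and the text gives no day on which it stops, so the window has no stated starting point in that arm. The arms could then be observed for different lengths of time.

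**Working it through.** The protocol gives no figure for the safety comparison, so there is none to reproduce. The check counts contacts, illustrates what unequal questioning could do, and then compares observation times.

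**1. Contacts in the eight treatment weeks (Day 8 to Day 64)**

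PRP sessions fall on Days 8, 15, 22, 29, 36, 43, 50 and 57, which makes 8.

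| Source for control frequency | Visits per week | Control contacts | Ratio to 8 PRP contacts |
|---|---|---|---|
| Control group section | 2 to 3 | 16 to 24 | 2.0 to 3.0 |
| Moist wound care section | 168/72 = 2.33 to 168/48 = 3.5 | 18.7 to 28 | 2.3 to 3.5 |

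Adding the Day 64 assessment to both arms gives (16+1)/9 = 1.9 to (24+1)/9 = 2.8 on the first source, and (18.7+1)/9 = 2.2 to (28+1)/9 = 3.2 on the second.

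Under the weekly rule in Safety, the count is 8 against 8, a ratio of 1.0.

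**2. Illustrative effect on recorded events at equal true rates**

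The documents give no capture rates, so these are assumptions. Let d be the chance that the diary captures an event, q the chance that one questioning elicits it (independently each time), and k the number of questionings per week. Then

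probability recorded = 1 − (1 − d)(1 − q)^k,

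with k = 1 for PRP and k = 2 or 3 for control.

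| d | q | PRP | Control, k = 2 | Control, k = 3 | Control ÷ PRP |
|---|---|---|---|---|---|
| 0 | 0.3 | 0.300 | 0.510 | 0.657 | 1.70 to 2.19 |
| 0 | 0.8 | 0.800 | 0.960 | 0.992 | 1.20 to 1.24 |
| 0.5 | 0.5 | 0.750 | 0.875 | 0.938 | 1.17 to 1.25 |
| 0.8 | 0.5 | 0.900 | 0.950 | 0.975 | 1.06 to 1.08 |

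As diary capture and elicitation improve, the ratio approaches 1: at d = 0.9 and q = 0.95 it is 1.00 to 1.01. In the least favourable row, the highest visit rate of 3.5 per week would give (1 − 0.7^3.5)/0.3 = 0.713/0.3 = 2.38.

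**3. The 30-day window**

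- PRP: last session Day 57, and 57 + 30 = Day 87. That is 87 − 64 = 23 days after the final assessment. Observation from Day 8 is 87 − 8 = 79 days.
- Control, if no window applies: observation ends on Day 64, and 64 − 8 = 56 days. The ratio is 79/56 = 1.41, which adds PRP events.
- Control, if study care is taken to stop on Day 64: 64 + 30 = Day 94, and 94 − 8 = 86 days against 79. The imbalance is smaller and runs the other way.

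The wording allows either reading.

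**The case against.** The strongest reply is that Safety, which sits under Outcome measures, already defines the comparison as weekly, and that Adverse effects covers only general vigilance and the reporting of serious reactions. That reading is reasonable, and under it the imbalance in questioning disappears. But the text does not say so. Adverse effects has the nurse enter whatever is reported at any appointment in the study database, and no sentence keeps those entries out of the comparison.

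Other points stand and limit the finding.

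- The diary is the same in both arms and reduces any bias by an unknown amount.
- The question is whether patients have experienced anything, so an event that resolved between visits can still be reported. A reader might suppose that a two-day event is noticed only if present at a visit. Detection would then be 2/7 = 29% under PRP and 2/3 = 67% to 100% under control, an apparent reduction of 57 to 71%. That ignores recall and the diary, and the documents do not support it.
- A reader might also infer that infection is certain to be under-recorded with PRP. The safety assessment of infection and exudate is scheduled only weekly, so this does not follow.
- The footnote under Table 2 leaves extra PRP visits open, which would narrow the ratio. It may belong to the control timetable.
- The final assessment on Day 64 could be taken as the end of study care in controls. The text does not say so, and on that reading the two arms still finish on different days.

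**Conclusion.** The point holds as a contradiction to be resolved. Two sections disagree on how often adverse effects are elicited. If the every-appointment rule feeds the comparison, controls are questioned about 2 to 3.5 times as often as PRP patients in the treatment weeks. This assumes that PRP patients attend only weekly.

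The effect on recorded events cannot be fixed from the documents. In the tabulated scenarios it runs from about 1.06 to about 2.2 times at equal true rates, and it could be negligible if diary capture is very good.

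It is tempting to conclude that the safety comparison as a whole is biased towards PRP. The documents do not support that: unequal questioning would favour PRP, but a window running for PRP only would work against it, so the net direction is undetermined. The plan should be corrected because the remedy is cheap and removes both imbalances.

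**What to change.** 1. State that the between-arm safety comparison uses the diary plus the weekly interview and wound assessment already described in Safety, on the same study days in both arms (Days 8, 15, …, 64).
2. Keep recording events that come up at additional visits. Report them in a separate listing and in an all-events table, so that none is lost.
3. End adverse-effect collection on one study day in both arms, for example Day 87, closed with one scripted telephone call.
4. Reconcile the footnote under Table 2 with the weekly schedule in the Intervention group section, and correct Table 1, so that the visit schedule in each arm is unambiguous.
5. Leave the reporting of serious reactions unchanged.

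The cost is a change of wording and forms, one call per patient, and slightly fewer events in the comparative table.
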